## Methods/Design

### Participants

Community-dwelling older adults aged 65 to 80 years without neurophysiologic diseases will be included in this single centre, randomised, controlled study. Figure 1 shows a flow chart of the study design. Eligibility will be screened with the Standard Assessment Protocol of the Acute Geriatrics Department at the University Hospital Basel / Felix Platter-Hospital Basel including demographic, anthropometric and medical data to rule out contraindications to exercise. Participants will be excluded when they reach cut-off scores for the following tests: Mini Mental State Examination score (MMSE, <24 points) [50,51], Clock Drawing Test (CDT, pathological test performance) [52], Tuning Fork test (individual vibration threshold) [53], Falls Efficacy Scale – International (FES-I, >24 points) [54], World Health Organisation Quality of Life Assessment-Bref (WHOQOL-Bref) [55], and the Freiburg Questionnaire of Physical Activity (FQoPA, less than 1 hour of everyday and sports-related physical activity per week) [56]. Evidence showed that even sedentary older adults are not at increased risk for injury when performing an exercise program compared to young adults [57]. Written informed consent will be obtained from all older adults prior to inclusion. This study is approved by the ethics committee of the University of Potsdam (reference number 34/2012), Germany, and will be conducted according to the ethical standards of the Helsinki Declaration.

**Figure 1 F1:**
[figure not shown]
Flow chart of study design.

### Questionnaires

#### Clock drawing test (CDT)

The CDT will be used for cognitive screening [58]. Participants will be asked to “Please draw a clock and write all the numbers and hands” on a pre-drawn circle of 10 cm in diameter. Afterwards they will be instructed to “Write down the time your clock shows as if it were in a schedule for trains or in a TV guide”. The CDT will be graded pathological if any mistakes in writing the numbers and hands, or writing down the time occur. Inter-rater reliability was shown to be high (IRR = .909) [52].

#### Falls efficacy scale – international version (FES-I)

Falls self-efficacy will be measured using the German 16-item FES-I [54]. This questionnaire measures the level of concern about falling during social and physical activities indoors and outdoors on a 4-point Likert scale (1 = not at all concerned to 4 = very concerned). Internal validity (Cronbach’s alpha = .96) and test-retest reliability (ICC = .96) have been shown to be excellent [59]. Additionally, a 12-months fall history will be collected at baseline.

#### World health organisation quality of life assessment-bref (WHOQOL-Bref)

Quality of life and general health will be assessed by 26 items on a 5-point Likert scale in four domains: physical health, psychological health, social relationship and environment [60]. Scores for the WHOQOL-Bref range from 0–100 with a higher score indicating better quality of life. For this study, the German version of the WHOQOL-Bref will be applied [61]. The WHOQOL-Bref performs according to international standards in terms of reliability, validity, test-retest, and sensitivity to change analyses [62].

#### Freiburg questionnaire of physical activity (FQoPA)

For the assessment of health-related physical activity, exercise, and estimation of energy expenditure we will apply the FQoPA [63]. Participants will be asked to report the amount of time spent in different activities during the past 7 days (everyday activities) and past month (sport and recreational activities). Energy requirements (MET) for physical activities are provided with the FQaPA allowing calculation of total weekly energy expenditure (<15 MET*h/week = “not active enough”, 15–30 MET*h/week = “meets basic public health recommendations for physical activity”, >30 MET*h/week = “satisfactory active”) [63]. The FQoPA has shown high test-retest reliability after 14 days and 6 months [56]. Validity of the FQoPA has been shown by correlating physical activity data with maximum oxygen uptake (r = .422) [56].

### Tuning fork test

A graduated Rydel-Seiffer tuning fork (Martin, Tuttlingen, Germany) will be used for testing vibration intensity at the internal malleolus of the dominant leg. The participants will be instructed to lie at ease in a supine position in a quiet, comfortably warm room. The tuning fork will be applied as perpendicular as possible resting on its own weight with the arms of the fork swinging maximally. Once the two arms are swinging, the fork vibrates at 64 Hz. Triangles with an arbitrary scale on calibrated weights at the extremities of the arms allow assessment of vibration threshold. When the participant indicates that vibration is no longer perceived, the point of intersection on the arbitrary scale (0 minimum to 8 maximum) is read. The readings of three repeated tests will be averaged and considered the vibration threshold. Pestronk et al. [53] were able to show that the Rydel-Seiffer tuning fork has high inter- and intrarater reliability.

### Balance and strength / power assessment

The primary outcome measures will be balance and strength / power at baseline (pre-test), after the intervention (post-test) and 12 weeks after the intervention (follow-up). In general, balance assessment will be performed before strength / power assessment to reduce interfering effects of muscle fatigue [64].

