**Methods/Design:**

Healthy old people (n = 54) between the age of 65 to 80 years will participate in this trial. The testing protocol comprises tests for the assessment of static / dynamic steady-state balance (i.e., Sharpened Romberg Test, instrumented gait analysis), proactive balance (i.e., Functional Reach Test; Timed Up and Go Test), reactive balance (i.e., perturbation test during bipedal stance; Push and Release Test), strength (i.e., hand grip strength test; Chair Stand Test), and power (i.e., Stair Climb Power Test; countermovement jump). Further, body composition will be analysed using a bioelectrical impedance analysis system. In addition, questionnaires for the assessment of psychosocial (i.e., World Health Organisation Quality of Life Assessment-Bref), cognitive (i.e., Mini Mental State Examination), and fall risk determinants (i.e., Fall Efficacy Scale – International) will be included in the study protocol. Participants will be randomized into two intervention groups or the control / waiting group. After baseline measures, participants in the intervention groups will conduct a 12-week balance and strength / power exercise intervention 3 times per week, with each training session lasting 30 min. (actual training time). One intervention group will complete an extensive supervised training program, while the other intervention group will complete a short version ('3 times 3’) that is home-based and controlled by weekly phone calls. Post-tests will be conducted right after the intervention period. Additionally, detraining effects will be measured 12 weeks after program cessation. The control group / waiting group will not participate in any specific intervention during the experimental period, but will receive the extensive supervised program after the experimental period.

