Dynamic steady-state balance will be tested while walking on an instrumented 10-m walkway using a two-dimensional OptoGait^©^-System (Bolzano, Italy). Participants will walk with their own footwear at self-selected speeds, initiating and terminating each walk a minimum of 2 m before and after the 10-m walkway to allow sufficient distance to accelerate to and decelerate from a steady-state of ambulation across the walkway. The rectangular OptoGait^©^-System is an opto-electrical measurement system consisting of transmitting and receiving bars for obtaining a two-dimensional measurement area. Each bar is 1 m in length and contains 100 LEDs that transmit continuously to each other. With a continuous connection between the two bars, any break in the connection can be measured and timed. The walking pattern will be monitored at 1,000 Hz, enabling spatial and temporal gait data to be collected. The OptoGait^©^-System demonstrated high discriminant and concurrent validity with a validated electronic walkway (GAITRite^©^-System) for the assessment of spatio-temporal gait parameters in orthopedic patients and healthy controls [67]. Hausdorff et al. [68] reported that spatio-temporal parameters of gait are important mobility markers in community-dwelling older adults. Thus, means and standard deviations (SD) of stride time, stride length, stride velocity, and stride width will be computed. In addition, coefficients of variation (CV) for stride time, stride length, stride velocity, and stride width will be calculated according to the following formula: [CV = (SD / mean) × 100] [69]. Of note, the CV is a sensitive and clinically relevant marker for increased fall risk [70]. Further, it has been reported that gait velocity below 70 cm/s is associated with an increased risk of falling in old community-dwelling adults [71]. Thus, using a stopwatch to the nearest 0.01 s, gait velocity will be assessed as a marker of fall risk. Granacher et al. [72] recently reported that intraclass correlation coefficient (ICC) values for the above reported gait parameters were above 0.75. To resemble real life situations, static and dynamic steady-state balance will be tested under single (standing / walking) and dual task (standing / walking while counting backwards aloud) conditions. The cognitive interference task will comprise an arithmetic task, in which the participants recite out loud serial subtractions by three starting from a randomly selected number between 300 and 900 given by the experimenter [73].

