### Statistics and sample size

An a priori power analysis was conducted to detect the sample size that is necessary to find statistically significant exercise effects [93] based on a study assessing the effects of balance training on postural control in older adults [94]. Considering a dropout rate of 10%, 18 participants per arm will be required to achieve 90% power (type II error of 0.10) with a type I error of 5%. Data will be analysed using a 2- and 3-way repeated measures analysis of variance (ANOVA) consisting of groups (INT1, INT2, CON) and time (pre-test, post-test, follow-up). Bonferroni post-hoc test will be used for statically significant (p < .05) group and time differences. Associations between clinical and biomechanical tests will be reported by their correlation coefficient (r value), level of significance (p value) and the amount of variance explained (r^2^ value). Values of r = 0.10 indicate a small, r = 0.30 a medium and r = 0.50 a large-size correlation [i.e., effect size] [95].

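### The primary outcome is two whole domains with no named variable or time point, and nothing controls error across roughly 60 candidate variables

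*Protocol article*

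**What the plan says.** The section Balance and strength / power assessment defines the primary outcome: "The primary outcome measures will be balance and strength / power at baseline (pre-test), after the intervention (post-test", with a third assessment 12 weeks later. The sections that follow describe the tests in each domain and the quantities taken from them. For gait, for instance, "means and standard deviations (SD) of stride time, stride length, stride velocity, and stride width will be computed", and coefficients of variation are added for the same four parameters. Standing and walking are both measured under single-task and dual-task conditions. None of these quantities, and none of the visits, is singled out as primary.

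Statistics and sample size specifies repeated measures ANOVA on group and time. Its only multiplicity provision is "Bonferroni post-hoc test will be used for statically significant (p < .05) group and time differences". The sample size statement reads "18 participants per arm will be required to achieve 90% power (type II error of 0.10) with a type I error of 5" per cent, after allowing for dropout ("Considering a dropout rate of 10" per cent). Its effect is "based on a study assessing the effects of balance training on postural control in older adults", with no variable, effect size or SD given. The abstract puts the total at 54.

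**The concern.** A 5% type I error describes one test. Here two domains are primary, each holds many variables, and each variable gets its own ANOVA at p < .05. The Bonferroni step works inside one variable, on pairs of groups or visits, and leaves the number of variables uncontrolled. A team following this plan could report as a primary result any variable that crosses .05, at either later visit, after seeing the data.

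The Discussion attaches practical weight to whether the short home programme proves effective, yet no variable is appointed to decide that. The sample size has the same gap: it rests on an effect on postural control, but the article does not say which balance variable carries the 90% power, and nothing is said about power for strength or power measures.

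**Working it through.** **1. The plan's own figure.** Three arms of 18 give 3 x 18 = 54, which matches the abstract. Allowing 10% dropout, 16/0.9 = 17.8, rounded up to 18, so about 16 per arm are evaluable. The 18 itself can be neither reproduced nor refuted, because no effect size, SD or variable is stated. Assuming a two-sided comparison of two means (normal approximation), the implied standardised effect is d = (1.960 + 1.282) x sqrt(2/16) = 1.15. One-sided it would be 1.04.

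**2. Counting the candidate variables**

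- Static balance: 4 tasks x 3 measures (two sway directions and standing time) x 2 task conditions = 24.
- Gait: (4 means + 4 SDs + 4 CVs + 1 stopwatch velocity) x 2 conditions = 26.
- Proactive balance: reach right, reach left, Timed Up and Go = 3.
- Reactive balance: two oscillation sums and the Push and Release score = 3.
- Strength/power: grip, chair stand, jump, stair climb = 4.

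The total is 60. If the stride SDs only feed the CVs and are not tested, it is 60 - 8 = 52. Taking one variable per test named in the abstract gives 10.

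**3. Independent tests, no true effect.** P(at least one p < .05) = 1 - 0.95^m.

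- m = 10: 40.1%
- m = 52: 93.1%
- m = 60: 95.4%, with 60 x 0.05 = 3 false positives expected

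**4. Correlated tests.** The article gives no correlations between individual variables, so a range was assumed. Data were simulated with no effect: 60 variables, 3 groups of 16, 3 visits, 2,000 runs per setting (simulation standard error at most sqrt(0.25/2000) = 1.1 percentage points). The blocks are the five sets in step 2. The last column requires a significant group x time F and also a favourable difference of either intervention arm from control in pre-to-post change, at a level corrected for three group pairs.

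| Assumed correlation | Any significant group x time F | Significant F and favourable corrected difference |
|---|---|---|
| None | 95% | 38% |
| Common 0.3 | 85% | 26% |
| Common 0.5 | 69% | 18% |
| Common 0.7 | 48% | 11% |
| Common 0.9 | 22% | 5% |
| Blocks: 0.5 within, 0 between | 83% | 27% |
| Blocks: 0.7 within, 0 between | 72% | 21% |
| Blocks: 0.8 within, 0 between | 62% | 17% |
| Blocks: 0.8 within, 0.3 between | 58% | 14% |

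The last column uses post-test contrasts only; adding follow-up contrasts would raise it.

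**5. Power under possible remedies**, at 16 evaluable per arm and d = 1.15, where d x sqrt(16/2) = 3.24.

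- One endpoint at 0.05: 3.24 - 1.96 = 1.28, power 90%.
- Two endpoints at 0.025 each: 3.24 - 2.24 = 1.00, power 84%.
- Bonferroni over 60 (0.05/60 = 0.00083): 3.24 - 3.34 = -0.10, power 46%.

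**The case against.** Several objections have force.

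- **A reader might infer that a false claim of benefit is close to certain.** The article does not support that. The 95% figure needs 60 independent tests and counts significance in either direction. A claim of benefit needs the favourable direction and, under the plan, a Bonferroni-corrected post-hoc difference. That combination is a minority event in every setting, and about 5% at a common correlation of 0.9.
- **A reader might also infer that correlation cannot help**, because the Background cites a finding of no significant association between steady-state, proactive and reactive balance. That bears only on correlation between balance domains. Of the 60 variables, 24 + 26 = 50 are steady-state measures, and many are linked by construction: the CV is SD over mean, stride velocity follows from stride length and time, and both sway directions come from one trial.
- **The count of 60 is a reading of the text.** The article says the gait means and SDs will be computed, not that each will be tested as primary, and the clinical tests also serve cross-validation. The ten-test figure is therefore given beside it.
- **The three visits do not triple the count**, since one group x time test spans them. What remains is that no visit is designated as deciding.
- **No success rule is stated.** That one significant variable suffices is an assumption of this check; the article does not exclude it.
- **A fuller protocol or analysis plan may name a primary variable.** That limits certainty. The point stands because the article does not merely leave the primary outcome open: it fixes it as two domains.

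**Conclusion.** The point holds. As written, the plan's 5% type I error belongs to single tests and to no conclusion about the trial. The chance of at least one significant group x time result is about 40% on the narrow count of ten independent tests. On 60 variables it is about 60% to 95% over most of the correlations tried, falling to 48% and 22% only at common correlations of 0.7 and 0.9.

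For a favourable corrected difference at post-test, 17% to 38% covers the range from strongly correlated blocks with no correlation between them up to independence. Stronger overall correlation gives less.

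These figures rest on assumed correlations, on no true effect anywhere, and on an any-one-variable reading of success. The defect itself, an unnamed primary variable and visit without control across variables, rests on the text alone.

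**What to change.** - Name one balance variable and one strength/power variable, both at post-test, as two primary endpoints, either of which may succeed. Test them with Holm at an overall 5%. Avoid calling them co-primary, a term usually taken to mean that both must succeed, in which case Holm would not be the matching procedure.
- State which balance variable the sample size rests on, and prefer it as the balance endpoint. The article does not identify it, so the sponsor must supply it.
- Make all other variables and the follow-up visit secondary, reported as estimates with 95% confidence intervals and without confirmatory claims.

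The cost is a change of wording and a small loss of power: about 84% per endpoint at 0.025, against 90%, at the effect implied by 16 evaluable per arm. Holm tests the second endpoint at 0.05 once the first succeeds, so 84% is the lower figure for a single two-group comparison. Pairwise correction among the three arms would reduce it further. The power statement should therefore be restated for the chosen endpoints and test. Correcting across all 60 variables instead would leave about 46% power, so naming endpoints in advance is the practical route.

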### Balance assessment and gait analysis

Static steady-state balance will be assessed using the Romberg Test and Sharpened Romberg Test [65] while standing on a force platform (Leonardo 105 Mechanograph®, Novotec Medical GmbH, Pforzheim, Germany, measurement error: ≤0.2%). Participants will have to perform 4 tasks with increasing level of difficulty: (1) standing in an upright position with feet closed and eyes open for 10 s without swaying while holding both arms extended to the front with palms facing upwards; (2) ditto, but with eyes closed; (3) ditto, but eyes open and feet in tandem stand; (4) ditto, but eyes closed and feet in tandem stand. Centre of pressure (CoP) displacements in medio-lateral (CoP_ml_s_ in mm) and anterior-posterior (CoP_ap_s_ in mm) directions as well as standing time during the different test conditions will be assessed. Test termination criteria are displacing feet, lowering arms or opening eyes. Besides CoP displacements, stand time will be recorded using a stopwatch to nearest 0.01 s. Age-specific corresponding norm values are 14 s to 15 s (female) and 14.3 s to 17.5 s (male) [65]. For the Romberg Test (eyes open, ICC = .86 and eyes closed, ICC = .84) and Sharpened Romberg Test (eyes open, ICC = .70 and eyes closed, ICC = .91) high test-retest reliability has been shown [66].

Dynamic steady-state balance will be tested while walking on an instrumented 10-m walkway using a two-dimensional OptoGait^©^-System (Bolzano, Italy). Participants will walk with their own footwear at self-selected speeds, initiating and terminating each walk a minimum of 2 m before and after the 10-m walkway to allow sufficient distance to accelerate to and decelerate from a steady-state of ambulation across the walkway. The rectangular OptoGait^©^-System is an opto-electrical measurement system consisting of transmitting and receiving bars for obtaining a two-dimensional measurement area. Each bar is 1 m in length and contains 100 LEDs that transmit continuously to each other. With a continuous connection between the two bars, any break in the connection can be measured and timed. The walking pattern will be monitored at 1,000 Hz, enabling spatial and temporal gait data to be collected. The OptoGait^©^-System demonstrated high discriminant and concurrent validity with a validated electronic walkway (GAITRite^©^-System) for the assessment of spatio-temporal gait parameters in orthopedic patients and healthy controls [67]. Hausdorff et al. [68] reported that spatio-temporal parameters of gait are important mobility markers in community-dwelling older adults. Thus, means and standard deviations (SD) of stride time, stride length, stride velocity, and stride width will be computed. In addition, coefficients of variation (CV) for stride time, stride length, stride velocity, and stride width will be calculated according to the following formula: [CV = (SD / mean) × 100] [69]. Of note, the CV is a sensitive and clinically relevant marker for increased fall risk [70]. Further, it has been reported that gait velocity below 70 cm/s is associated with an increased risk of falling in old community-dwelling adults [71]. Thus, using a stopwatch to the nearest 0.01 s, gait velocity will be assessed as a marker of fall risk. Granacher et al. [72] recently reported that intraclass correlation coefficient (ICC) values for the above reported gait parameters were above 0.75. To resemble real life situations, static and dynamic steady-state balance will be tested under single (standing / walking) and dual task (standing / walking while counting backwards aloud) conditions. The cognitive interference task will comprise an arithmetic task, in which the participants recite out loud serial subtractions by three starting from a randomly selected number between 300 and 900 given by the experimenter [73].

Proactive balance will be assessed using the Functional Reach Test (FRT) [74] and the Timed up and Go Test (TUG) [75]. The FRT measures the maximal distance one can reach forward beyond arm’s length while maintaining a fixed base of support in the standing position. Maximal reach distance of the right and left arm will be recorded, whereas a distance between 15.4 cm to 25.4 cm indicates a moderate risk for falls [76]. The FRT will be measured while standing on a force platform (Leonardo 105 Mechanograph®) which additionally allows collection of CoP displacements. The FRT showed excellent test-retest reliability (ICC = 0.92) in older adults [74]. Validity of the FRT has been proved by Newton RA [77] when testing healthy community-dwelling older adults.

The TUG will be applied as described by Podsiadlo and Richardson [75]. Participants will be asked to perform the TUG at their self-selected habitual walking speed. One practice and one test trial will be performed. Time will be recorded with a stopwatch to the nearest 0.01 s. Before testing, a trained evaluator will provide standardized verbal instructions regarding the test procedures. Participants will be seated and instructed to walk 3 m, turn around, walk back to the chair and sit down. The stopwatch will be started on the command “ready-set-go” and stopped as the participant sits down. The TUG showed excellent test-retest reliability (ICC = 0.99) in older adults [75].

During the reactive balance test, participants will stand in bipedal step stance on a two-dimensional balance platform (Posturomed, Haider, Bioswing, Pullenreuth, Germany). The platform is mounted to four springs and is free to move in the transversal, ml, and ap directions. The maximal natural frequency of the Posturomed is below 3 Hz. The mechanical constraints and the reliability of the system were described earlier [78]. If the platform is in neutral position, the maximum range of motion in the ap and ml directions amounts to 70 mm, respectively. Medio-lateral perturbation impulses will be applied in order to investigate reactive postural control of the participants. Therefore, the platform will be moved 2.5 cm from the neutral position in the ml direction, where it will be magnetically fixed. For experimental testing, participants will be asked to stand (i.e., bipedal step stance) in erect position with hands placed on hips and gaze fixated on a cross on the nearby wall. Three to five trials help participants to get accustomed to the measuring device. After investigators visually control the position of the subjects, the ml perturbation impulse will unexpectedly be applied by detaching the magnet. The platform suddenly accelerates in the medial direction. The participants’ task is to damp the oscillating platform by balancing on the Posturomed. Summed oscillations of the platform in medio-lateral (SOml_r) and anterior-posterior (SOap_r) directions will be assessed by means of a joystick like 2D potentiometer (Megatron) which is connected to the platform. The potentiometer measures the position of the platform in degree [°]. The signal will be differentiated, rectified, and integrated over the 10 s test interval. Three trials will be performed. The best trial (least oscillations in ml direction) will be used for further analysis. Muehlbauer et al. [26] reported ICC values of 0.69 for SOml_r and 0.40 for SOap_r.

As a corresponding clinical test for reactive balance, the Push and Release Test (PRT) will be conducted. The PRT rates the postural response to a sudden release of a participant pressing backward on an examiner’s hands placed on a participant’s back [79]. The participant is instructed to stand in a comfortable stance with his or her eyes open and push backward against the palm of the examiners’ hands. After the examiner suddenly releases his or her hands, the participant is required to regain balance (backward stepping until a proper position is reached). During testing, the examiner will be responsible for safety of the participant. For rating purposes, the actual amount of steps to regain balance (not those to reorient the feet) will be measured (0 = 1 step, 1 = 2–3 small steps backwards with independent recovery, 2 = ≥4 steps with independent recovery, 3 = steps with assistance for recovery, 4 = fall or unable to stand without assistance). The PRT showed high test-retest reliability (ICC = 0.84) with a sensitivity of 89% and a specificity of 85%.

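### Romberg stands are set at 10 s beside stand-time norms of 14 to 17.5 s, and CoP displacement in mm, with no stated time normalisation, can look better when a trial ends early

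*Protocol article*

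**What the plan says.** The protocol article, under Balance assessment and gait analysis, lists four Romberg and Sharpened Romberg tasks on a force platform. The first is "standing in an upright position with feet closed and eyes open for 10 s without swaying". The other three repeat it with changes to vision and foot position only, the last being "ditto, but eyes closed and feet in tandem stand".

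Two kinds of measure are taken:
- CoP: "Centre of pressure (CoP) displacements in medio-lateral (CoP_ml_s_ in mm) and anterior-posterior (CoP_ap_s_ in mm) directions".
- Time: "Besides CoP displacements, stand time will be recorded using a stopwatch to nearest 0.01 s".

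On when a trial ends, the text says: "Test termination criteria are displacing feet, lowering arms or opening eyes". It then gives reference times for stand time: "Age-specific corresponding norm values are 14 s to 15 s (female) and 14.3 s to 17.5 s (male". It does not say which task these belong to or whether a stand may continue past 10 s.

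For the reactive balance test, the same section does fix the measurement interval: "The signal will be differentiated, rectified, and integrated over the 10 s test interval". The section on balance and strength / power assessment makes balance part of the primary outcome, and the Romberg tasks are the only static steady-state balance test. They are also run under dual-task conditions.

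**The concern.** There are two separate problems.

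**Duration against norms.** A 10 s stand and norms that begin at 14 s cannot both describe one stand time. If 10 s is the maximum, no participant can reach the norms, and stand time is blind to any gain beyond 10 s. That loss occurs at data collection, so no later analysis can recover it. If 10 s is not the maximum, the stated duration is misleading and trial length is open-ended.

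**CoP over unequal trial lengths.** Several common sway measures in mm grow with the length of the recording. A participant who fails early may then have a smaller value than one who completes the stand with the same sway. Training that lengthens the stand could show as unchanged or worse CoP. The article also plans to correlate clinical with biomechanical tests. If stand time is paired with such a CoP measure, shorter stands mechanically produce smaller values and distort the correlation.

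**Working it through.** The plan derives no figure on this point, so there is nothing of its own to reproduce.

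**Step 1: duration against norms.** Inputs, all from the Romberg paragraph: stand of 10 s; norm limits of 14 and 15 s (female), 14.3 and 17.5 s (male). Largest attainable share = 10 / norm; shortfall = norm − 10.

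| Norm limit | 10 / norm | Shortfall |
|---|---|---|
| 14 s | 0.71 | 4.0 s |
| 14.3 s | 0.70 | 4.3 s |
| 15 s | 0.67 | 5.0 s |
| 17.5 s | 0.57 | 7.5 s |

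If 10 s is the maximum, every norm limit is out of reach.

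**Step 2: how CoP measures depend on trial length.** The article does not define the CoP metric, so four candidates were compared. Sway was simulated as a stationary process of constant intensity. The assumptions, none from the article, were SD 5 mm, time constants 1 s and 0.15 s, and 3000 runs. Each entry is the mean value when the trial stops at that time, divided by the mean value at 10 s.

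| Metric | 2.5 s | 5 s | 7.5 s |
|---|---|---|---|
| Cumulative path (mm) | 0.25 | 0.50 | 0.75 |
| Range (mm) | 0.58 | 0.79 | 0.91 |
| Within-trial SD (mm) | 0.70 | 0.88 | 0.95 |
| Mean velocity (mm/s) | 0.99 | 1.00 | 1.00 |

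All three measures in mm fall in shorter trials although sway is identical. The per-second measure does not.

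**Step 3: how large a real difference could be hidden (cumulative path only).** Let one participant sway k times as fast and fail at T seconds, against a full 10 s trial at the reference speed. The path ratio is k × T / 10, which is below 1 when T < 10 / k:
- k = 1.5: 10 / 1.5 = 6.7 s
- k = 2: 10 / 2 = 5 s
- k = 3: 10 / 3 = 3.3 s

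On this metric, a participant swaying twice as fast scores better than a completer if the trial ends before 5 s.

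**The case against.** The strongest reply is that 10 s is never called a hard stop. Elapsed time is not among the termination criteria, and timing to 0.01 s beside norms of 14 to 17.5 s fits a stand that may run longer. A reader might therefore infer too much in concluding outright that every participant must fall below the norm; that holds only if 10 s is the maximum. But if the stand runs on, the stated duration needs correcting and trial lengths vary more, which sharpens the CoP problem. The paragraph needs reconciling on either reading.

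Second, the article only lists the norms. It grades nobody by them, unlike the Chair Stand Test, and no stated analysis uses them. This stands: the mismatch affects interpretation and corrupts no planned test.

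Third, the CoP metric is undefined, and a condensed article may leave the handling of incomplete trials to the full protocol. A reader might infer that the measure always rewards early failure. The text does not support that. The effect is full only for cumulative path and weaker for range and SD, it is absent for a per-second measure, and a large excursion at the moment of failure could offset it for range. What remains is that the article specifies mm alone here, while it fixes the interval for the reactive test.

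Fourth, the two problems fall largely on different tasks. Where everyone completes 10 s, trial lengths are equal and CoP is unaffected; where people fail early, stand time still registers improvement. This also stands, and because stand time is already recorded for each condition, an early failure would be visible there.

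**Conclusion.** The point holds in a conditional form and should be corrected. The 10 s duration and the 14 to 17.5 s norms are unreconciled. With 10 s as the maximum, the shortfall is 4.0 to 7.5 s and gains beyond 10 s go unseen.

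CoP in mm can favour earlier failure. At equal sway and a stop at 5 s, the value is 0.50 to 0.88 of the full-trial value, depending on the metric. These ratios rest on the assumed sway process and exclude any excursion at failure.

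The size of the effect in this trial cannot be computed, because no failure rates are given. It is likely to matter most in the tandem, eyes-closed and dual-task stands. A reader might also infer that stand time must pile up at its maximum and so cannot be analysed by ANOVA. That is plausible on the easier tasks but depends on the same missing rates. The consequence is limited to one test among many within the primary outcome, although it is the only static steady-state one.

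**What to change.** 1. Analyse CoP as mean velocity (mm/s over the time actually stood) and report it alongside stand time.
2. Settle the duration in one of two ways. Either let the stand run to a stated cap above 17.5 s, with CoP taken per second or over a fixed window (stands shorter than the window still need the per-second form), or state that 10 s is the maximum and drop the norm comparison. If norms are kept, name the task they apply to.
3. If stand time does pile up at the cap on the easier tasks, analyse it there as completed / not completed rather than by ANOVA.

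Cost: wording in the test manual and analysis plan, and at most a few more seconds per stand. The downside is that values in mm/s are not directly comparable with studies that report mm; showing the mm values descriptively for completed stands would keep that link.
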